### Interim analyses {21b}

N/A. No interim analyses are planned.

### Methods for additional analyses (e.g., subgroup analyses) {20b}

N/A. No additional analyses are planned.

### Methods in analysis to handle protocol non-adherence and any statistical methods to handle missing data {20c}

Protocol violations after randomization will be listed in the Clinical Study Report, tabulated by subject and recruitment site. We will perform intention-to-treat analyses with a “missing=failure” strategy to the management of missing data.

Sensitivity analyses will be performed for the missing data management: multiple imputation, available data, and maximum bias.

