### Outcomes {12}

The primary outcome will be phonation-related disability based on the overall score of the Voice Handicap Index (VHI) [14, 15] at 1 month after delivery of either prosthesis. This ranges from 0 and 120; the VHI includes 30 items exploring functional, emotional, and physical domains. The secondary outcomes include the Deglutition Handicap Index (DHI, 30 items, maximum score 120) and the EORTC QLQ-C30 (a general questionnaire containing the QLQ-H&N35 modules [35 items in all] exploring the health-related quality of life) prepared by the European Organization for Research and Treatment of Cancer (EORTC) [16–18]. Both questionnaires are scored from 0 to 100 and will be evaluated at 1 month after the delivery of either prosthesis. All questionnaires have been translated into French and validated.

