### Sample size {14}

Sample size calculation is based on the average comparison of crossover tests: the *t*-test for difference of means in 2 × 2 crossover design (N-Query software). We assume that the use of the rigid obturator will be associated with a mean VHI score of 34 and a standard deviation of 15 [14, 15]. To ensure a power of 90%, an alpha risk of 5%, and an expected difference of 15 points between the reference and new obturator, 7 patients per treatment sequence are required, thus 14 in all. No drop-out was included in the sample size calculation due to the small duration of the study follow-up (3 months).

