## Statistical methods

### Statistical methods for primary and secondary outcomes {20a}

Scores will be evaluated in terms of mean, standard deviation, median, range, and first and third quartiles. To assess the results, a mixed-effects linear regression model will be used to analyze effects of “treatment” and “period.” Analyses will vary by whether an interaction between treatment and period is or is not apparent. The response variable of the linear regression model will be the overall VHI score; the explanatory variables will be the treatment group (a fixed effect), the administration period (a fixed effect), the interaction between treatment and period (a fixed effect), and the patient (a random effect). The same statistical methods will be used for the secondary outcomes.

Sensitivity analyses will be performed by adding “interaction treatment*period.”

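### The main missing-data rule, missing = failure, does not fit a continuous VHI score; with 14 patients, one inserted value can cost almost no power or nearly all of it

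*Protocol article*

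**What the plan says.** The protocol article, section {20c} on non-adherence and missing data, sets the main strategy: "We will perform intention-to-treat analyses with a “missing=failure” strategy to the management of missing data". It adds: "Sensitivity analyses will be performed for the missing data management: multiple imputation, available data, and maximum bias".

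The outcome is a score. Under Outcomes {12} the primary outcome is the "overall score of the Voice Handicap Index (VHI) [14, 15] at 1 month after delivery of either prosthesis", and of its scale the section says: "This ranges from 0 and 120; the VHI includes 30 items exploring functional, emotional, and physical domains". Under Statistical methods {20a}: "The response variable of the linear regression model will be the overall VHI score". The same methods apply to the secondary scores.

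Three other sections bear on the point:
- Sample size {14} arrives at 7 patients per sequence, 14 in all, and makes no allowance for drop-out.
- Section {11b} counts a participant who declares not using the obturator as a drop-out.
- Section {18a} has the VHI collected at baseline as well as after each device.

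**The concern.** With a binary endpoint, missing = failure is a complete instruction, because the missing patient is counted as a non-responder. With a 0 to 120 score it is not. Somebody must choose a number, and the model then treats that number as a measurement. The article defines no VHI threshold, responder or failure from which a number would follow.

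In a within-patient comparison of 14 people, one extreme value shifts the mean difference and also inflates its standard error. The primary result could then turn on whether one person missed one visit, in which period, and what number was inserted. The rule is not reliably cautious either: a missing score under the rigid obturator makes the new device look better.

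**Working it through.** **Inputs.** From Sample size {14}: "a mean VHI score of 34 and a standard deviation of 15" under the rigid obturator, and "To ensure a power of 90%, an alpha risk of 5%, and an expected difference of 15 points between the reference and new obturator"; N = 14. The expected membrane mean is therefore 34 − 15 = 19. My assumptions are a two-sided 5% test and a within-patient correlation of 0.5, since the article states neither.

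**Step 1: reproduce the plan's figure.** SD of the within-patient differences = 15 × √(2 × (1 − 0.5)) = 15. Noncentrality = 15 / (15/√14) = 3.74 on 12 df, which gives 92.9% power. N = 12 gives 87.6%, so 14 is the smallest even number reaching 90%. The figure reproduces on this reading. If 15 were the within-patient SD, the SD of differences would be 21.2 and power at N = 14 would be 68%.

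**Step 2: expected estimate with inserted values of 120.** Each complete pair contributes 15 points of benefit. A pair with the membrane score set to 120 contributes 34 − 120 = −86. A pair with the rigid score set to 120 contributes 120 − 19 = +101.

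- One membrane score: (13 × 15 − 86)/14 = 7.8
- Two membrane scores: (12 × 15 − 2 × 86)/14 = 0.6
- Three membrane scores: (11 × 15 − 3 × 86)/14 = −6.6
- One rigid score: (13 × 15 + 101)/14 = 21.1

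**Step 3: power, by simulation** of the period-adjusted crossover t-test under the same assumptions.

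| Data set | Power to favour the membrane |
|---|---|
| Complete | about 93% |
| One membrane score set to 120 | about 1.5% |
| set to 90 | about 19% |
| set to 80 | about 33% |
| set to 60 | about 63% |
| set to 49 | about 76% |
| set to 34 | about 88% |
| set to the patient's own rigid score | about 90% |
| left out | about 90% |
| One rigid score set to 120 | about 87% |

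At 120 the standard error rises from 3.9 to 8.2. The test statistic is then typically near 7.8/8.2 = 0.95, against a critical value of 2.18. Across correlations of 0.7 to 0.3, power at 120 is 1.3% to 1.8%. Keeping simulated scores within 0 to 120 lowers it to about 1%.

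**Step 4: direction.** With one membrane score at 120, the estimate changes sign in about 3% of simulated trials and is never significant for the rigid device. With two, the sign is negative in about 44%; with three, in about 95%.

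**Step 5: no true difference (both means 34).** One rigid score at 120 produces an apparent membrane benefit of (120 − 34)/14 = 6.1 points. The larger standard error keeps false-positive findings for the membrane at about 1.8%, below the nominal 2.5% on that side. The damage is to the estimate, not to the type I error.

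**Step 6: how likely is a missing score?** The article gives no rate. If 2%, 5% or 10% of patients had one, the chance of at least one among 14 would be 1 − 0.98¹⁴ = 25%, 1 − 0.95¹⁴ = 51% or 1 − 0.90¹⁴ = 77%.

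**The case against.** **The value 120 is not in the document.** This stands. Section {20c} lists maximum bias separately. If that undefined term means worst-case imputation, a main rule of 120 would largely duplicate it, so a milder value may be meant. With a mild value the loss is small, which is why the result has to be given as a range. A full protocol or SAP may also state the number, so the absence of a number is not the point. The point is that the stated rule does not fit the endpoint; whatever number is chosen would still be an invented score analysed as observed.

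**A reader might infer that one missing membrane score could turn the evidence against the membrane device.** The figures do not support this. Even at 120 the expected estimate still favours the membrane by 7.8 points. It takes about two such scores to cancel the effect and three to reverse its sign.

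**The safeguards are already planned.** Available-data and multiple-imputation analyses would expose a result driven by one value. That is true, but they are only sensitivity analyses. If they disagreed with the main analysis, the ill-fitting rule would still supply the primary result.

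**An unfavourable value may be justified.** Section {11b} turns declared non-use into drop-out, so a missing score can reflect failure of the device, and missing-at-random is open to question. This stands. It is a reason to keep a failure-type analysis with a defined value, but not to make an undefined one primary.

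**Conclusion.** The point holds in a conditional form. The main missing-data rule was made for success/failure endpoints and is applied to a continuous score for which no failure is defined. With N = 14 and no drop-out allowance, one missing membrane score leaves power anywhere from about 1.5% (value 120) to about 90% (the patient's own rigid score), against about 90% if the score is left out. In the other direction, one rigid score at 120 inflates the estimated benefit from 15.0 to about 21 points.

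These figures rest on means of 34 and 19, SD 15, correlation 0.5 and a two-sided 5% test. They apply only if a score is in fact missing. The mismatch between rule and endpoint depends on none of these assumptions.

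**What to change.** In section {20c}, make the primary analysis the planned linear mixed model fitted to all observed scores of all randomised patients, without imputation. This is the plan's own available-data analysis, and the random patient effect already accommodates a patient with one period missing. Apply the same rule to the DHI and EORTC scores.

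Move missing = failure to the sensitivity analyses with a stated number for each score. For the VHI this could be the patient's own baseline value, which section {18a} collects, with 120 as the extreme case. Keep multiple imputation and maximum bias.

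The cost is a small rewording of one section, with no new data and no extra patients. The real price is that the primary result then relies on missing-at-random, which section {11b} makes doubtful. The report should therefore show the failure-type, multiple-imputation and maximum-bias results beside it and say whether the conclusion survives.

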### Plans to give access to the full protocol, participant-level data, and statistical code {31c}

The full protocol, participant-level data, and statistical code are available upon request and after a contract has been put in place to ensure, among other things, that the recipient complies with the GDPR.

## Oversight and monitoring

### Composition of the coordinating center and trial steering committee {5d}

The steering committee is made up of the following people: [name] [name] (chairman, principal investigator), [name] [name] (clinical investigator and responsible for the obturator manufacturing), [name] [name] (clinical investigator and responsible for the center of Toulouse), [name] [name] (methodologist), a statistician, [name] [name] (pharmacist), and a representative of the sponsor. This committee checks ethics. With the Center for Methodology and Data Management, this committee checks also the status of the research, possible problems, and available results. It decides on any relevant modification of the protocol necessary for the continuation of the research. It may propose to extend or interrupt the research.

### Composition of the data monitoring committee, its role, and reporting structure {21a}

The establishment of a data monitoring committee is not necessary for this study, which does not entail any particular risk a priori for the participants.

### Adverse event reporting and harms {22}

Adverse events that may occur will be monitored by the investigators and a research assistant. Possible adverse events include ingestion/inhalation of imprint materials, metal pins, resin, or prosthesis or membrane materials; oral injury; and allergies to acrylic resin, chrome-cobalt (of the metal pins), or latex.

### Frequency and plans for auditing trial conduct {23}

In the context of the data monitoring plan, a clinical research assistant mandated by the sponsor will visit each investigating center on a regular basis, during the implementation of the research, one or more times during the research according to the rhythm of the inclusions and at the end of the research. An audit can be conducted any time at the request of the sponsor and independent from the investigators, but also at the request of the competent health authority.

### Plans for communicating important protocol amendments to relevant parties (e.g., trial participants, ethical committees) {25}

Any important protocol amendment must obtain, prior to its implementation, a favorable opinion from a French Ethics Committee for Person Protection (Comité de Protection des Personnes [CPP]) and an authorization from the French National Agency for Drug Safety (Agence Nationale de Sécurité du Medicament et Produits de Santé [ANSM]). All modifications to the protocol should be brought to the attention of all investigators participating in the research. Any modification that modifies the coverage of participants or the benefits, risks, and constraints of the research is the subject of a new information sheet and a new consent form.

## Dissemination plans {31a}

Results of the trial will be communicated to the participants through a brochure that will be sent at the patient’s home. They will be also submitted to national and international journals for publication.

Results of the trial will be communicated to the participants upon request to the investigator.

## Discussion

Our hypothesis is that the new membrane obturator will improve speech more than the standard obturator [19]. The primary outcome is therefore the Voice Handicap Index (VHI) score. This dysphonia self-assessment scale quantifies the extent to which a phonation disorder compromises the quality of life and assesses the psychosocial consequences. The French version has been validated and used in patients with oropharyngeal cancer [14, 20]. The Deglutition Handicap Index (DHI) is a derivative of the VHI that focuses on swallowing [18]. This questionnaire quantifies the adverse effects of swallowing disorders and the score will serve as a secondary outcome.

Soft palate defects arise in various ways. However, we will include only patients who have undergone surgical tumor removal. Soft palate trauma is very rare. Patients with congenital defects such as palatal clefts usually develop mechanisms that compensate for speech and swallowing difficulties; these become entrenched and are difficult to bypass. Oncology patients should be able to adapt to the use of a new device; our new prosthesis should restore speech and improve swallowing, improving the quality of life [19].

“Quality of life” includes physical components (autonomy and physical activities), psychological components (anxiety, depression, and emotion), relational components (family, social, and professional), symptomatic components (repercussions of the disease and treatment thereof), and other components (sexuality and self-image). The relevant psychometric tools (scales or questionnaires) are easy to use and well standardized. The QLQ-H&N35/EORTC QLQ-C30 questionnaires of the EORTC are commonly used for ear-nose-and-throat assessments [16, 17, 21, 22]. French versions have been employed to evaluate patients with oropharyngeal cancers [21, 23, 24]. Both questionnaires yield several scores (thus not single overall scores) and therefore cannot serve as principal assessment criteria. In addition, they explore aspects of the quality of life that are not related to our intervention. We will perform secondary analyses only.

The crossover design is optimal for several reasons:
The two prostheses are removable and their effects do not persist. Thus, the initial state is re-attained at the beginning of the second period; no “washout” is requiredThere is no further substance loss over the test periodThe risk of loss to follow-up is minimal; the test periods are short (1 month)Outcomes of interest will be measured at 1-month intervals; no conditioning effect is in play

This study will yield high-quality evidence on the utility of a new device that should greatly improve the management and the quality of life of patients with acquired velar insufficiencies. Such insufficiencies cause malnutrition, reduce the quality of life, can lead to patient refusal to accept care, and may trigger psychological and social isolation associated with poor communication and societal integration [8, 25]. Often, the rigid obturator does not restore oronasal partitioning; the patient remains disabled. The membrane obturator will remedy swallowing and phonation deficiencies more effectively and rapidly than a rigid obturator.

## Trial status

This trial is registered as CHUBX 2018/34. This report is based on protocol version 1.0. Recruiting has started in July 2020 and continues for 21 months. Due to the COVID-19 crisis, the initial deadline of April 2022 may be delayed of few additional months (to be determined).

## Abbreviations

ANSM: Agence Nationale pour la Sécurité du Médicament et des Produits de Santé ([French] National Agency for Medicines and Health Products Safety)
CONSORT: Consolidated Standards of Reporting Trials
CPP: Comité de Protection de Personnes ([French] Ethics Committee for the Protection of Persons)
CRF: Case report form
CHU: Centre Hospitalo-Universitaire (University Hospital Center)
CTU: Bordeaux University Hospital Clinical Trial Unit
